### Sample size calculation

2.8

Our literature review indicated that the AE rate within 3 months after hospitalization for AECOPD is approximately 48.9% (5). Our preliminary data (unpublished) indicate that after VIT, the treatment failure rate at 90 days is approximately 15%. Therefore, the expected effect size between the two groups is about 33.9%. We set the significance level α = 0.05 and the statistical power at 80% (i.e., β = 0.20), with a dropout rate assumed to be 20%. The calculated values for *Z*_α_/2 and *Z*β are 1.96 and 0.84, respectively, with standard deviation σ = 0.614, effect size Δ = 0.339. Based on these parameters and sample size calculations, each group must include ≥32 patients. To ensure data accuracy and account for potential dropouts, we plan to recruit 40 patients per study group, totaling 80 participants.

### AE reporting

2.9

Since this study will only involve nonpharmacological, low-risk inhaler technique education interventions, we do not expect serious intervention-related adverse events. The research team will closely monitor participants to collect, assess, and report any adverse events or other unintended effects actively or spontaneously reported during the interventions.

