Numerous studies have confirmed that an improper inspiratory flow rate—too low or too high—can hinder drug delivery (3, 10). The most commonly used parameter for assessing the inhalation technique is peak inspiratory flow rate (PIFr); it is the maximum flow rate generated by a patient during inhalation to overcome the internal resistance of an inhaler (6). Different types of inhalers, such as pressurized metered dose inhaler (pMDI), dry powder inhaler (DPI), and soft mist inhaler (SMI), have varying PIFr requirements because of varied drug particle release mechanisms and device resistance. The optimal inspiratory flow rate for DPIs is approximately 60 L/min, which generates turbulence inside the device, facilitating the dispersion of the powder into fine particles that can be carried into the airways via airflow (11). In contrast, pMDIs and SMIs do not rely on the patient's active inhalation to generate turbulence for drug particle release and thus have an optimal inspiratory flow rate of about 30 L/min (12). If a patient's measured PIFr is suboptimal, it may limit medication delivery to the lower airways, thereby reducing efficacy (13). In addition to inspiratory flow rate, proper inhalation techniques are crucial for drug deposition. Adequate exhalation before inhalation minimizes residual volume, increasing the volume of medicated air inhaled and enhancing drug delivery to small airways. Furthermore, prolonging breath-holding after inhalation facilitates the deposition of fine drug particles in small airways via Brownian motion, reducing the proportion of exhaled suspended particles (14).

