**Assessment of physical function**						
Grip strength				✓		✓
MVC of Knee extension				✓		✓
6MWT				✓		✓

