**Questionnaire**						
mMRC				✓		✓
CAT				✓		✓
TAI		✓				✓
EXACT-PRO					✓ (daily)	
Frequency and severity of AE					✓ (weekly)	

PIFr, peak inspiratory flow resistance; EIT, effective inspiratory time; EIV, effective inspiratory volume; IIFSC, integrated inspiratory flow system score; IOCL, inhalation operation chick list; MIP, maximum inspiratory pressure, MEP, maximum expiratory pressure, MVC, maximal voluntary contraction; 6MWT, 6 minutes walking test; mMRC, modified medical research council dyspnea scale; CAT, COPD assessment test; TAI, test of the adherence to inhalers; EXACT-PRO, exacerbation of chronic pulmonary disease tool-patient reported outcome; AE, acute exacerbations.

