### Interventions

2.4

All patients will receive two inhaler usage instruction sessions during hospitalization and will be followed up weekly via telephone over 12 weeks after discharge. Researchers blinded to the group assignments will implement this measure. It will ensure regular use of inhalation medications in both groups during the study period and enable recording of any possible AE events and their severity.

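### Section 2.9 ties adverse-event collection to the interventions, so non-fatal events other than exacerbations have no stated collection after discharge or at the week-12 tests

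*Protocol article*

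**What the plan says.** Section 2.9 of the protocol article calls the training low-risk and adds that "we do not expect serious intervention-related adverse events". It then states what will be collected: "any adverse events or other unintended effects actively or spontaneously reported during the interventions".

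Section 2.4 describes what patients receive: "two inhaler usage instruction sessions during hospitalization and will be followed up weekly via telephone over 12 weeks after discharge". It says the calls will "enable recording of any possible AE events and their severity". The footnote to Table 1 gives the abbreviation: "AE, acute exacerbations". Section 2.6 describes the same calls as asking about respiratory symptoms over the past week and reminding patients to take their medication.

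Table 1 ticks both interventions at baseline (V0) only and gives follow-up a column of its own. It has no row for adverse events. The block headed "Assessment of physical function" (grip strength, knee-extension strength and the 6-minute walk) is ticked before discharge (V2) and at V3, as are the maximal respiratory pressures.

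**The concern.** An adverse-event window should cover the time in which the intervention could do harm and the time in which study procedures are carried out. Here the teaching takes place in hospital, but patients use what they were taught at home. The Background says a poor inspiratory flow matters in use: "If a patient's measured PIFr is suboptimal, it may limit medication delivery to the lower airways, thereby reducing efficacy". The Discussion adds that too high a flow with a pMDI or SMI puts more drug in the oropharynx. A local effect of that kind would arise during home use, and no listed outcome is designed to record it.

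Effort-dependent tests are repeated at V3 in patients who were in hospital with an exacerbation 12 weeks earlier. An injury or other event during one of them also falls outside a window that ends with the interventions.

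At stake is the completeness of the safety report. If the wording is followed literally, a short list of adverse events could reflect where the window was placed and could not be read as support for the low-risk statement. The abbreviation adds a smaller risk: Section 2.9 is headed with AE, which stands for acute exacerbation in the rest of the article.

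**Working it through.** The plan gives no figure for the length of the adverse-event window, so there is none to reproduce. The check sets the sections side by side and then sizes the gap.

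**What counts as the interventions**
- Section 2.1 says participants are assigned to interventions and follow-up, naming the two separately.
- Table 1 ticks the interventions at V0 only and shows follow-up as a separate column.
- Section 2.4 places the two teaching sessions in hospital. The weekly calls are described under the same section heading.

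The first two favour a window that closes before discharge. The heading of 2.4 leaves room for a wider one.

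**What is collected from discharge to week 12, in both arms**

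| Event | Stated collection |
|---|---|
| Exacerbation | Weekly call (2.4, 2.5.1) |
| Exacerbation with hospitalization or emergency visit | Severity grading (2.5.2) |
| Respiratory symptoms | Daily EXACT-Pro (2.5.2, 2.6) |
| Death from any cause | Secondary outcome (2.5.2) |
| Hospitalization for other lung disease | Withdrawal criterion (Table 2); no text requires it to be reported as an adverse event |
| Non-fatal, non-pulmonary hospitalization | None stated |
| Local effect of the inhaled drug | None stated |
| Event during a V3 physical test | None stated |

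**Share of study time outside the literal window**
- Study period (2.1): 1 week before discharge plus 12 weeks after = 7 + 84 = 91 days, approximately.
- If the whole pre-discharge week counts as intervention time: 84/91 = 92.3% outside.
- If only the sessions count, on at most two days: (91 − 2)/91 = 89/91 = 97.8% outside.

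The article does not give the session dates, so the range is about 92% to 98%. The lower figure is the safer one to cite.

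**Contacts already planned**
- 80 patients (2.8) × 12 weekly calls (2.4) = 960 calls if everyone is retained.
- With the 20% dropout assumed in 2.8, and counting no calls from those who drop out: 80 × 0.8 × 12 = 768.

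A wider window therefore needs no new contacts.

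**The case against.** The strongest objection is that the likeliest harm of poor teaching is already measured. If retraining left patients inhaling less drug, this should show in exacerbations, their severity, daily symptoms, mortality, lung function, mMRC and CAT. The technique itself is re-measured at V1 and V3. All of this is recorded in both arms. The point stands. A reader might infer from 2.9 that the trial is bound to report no harm, and the documents do not support that: the main route to harm is covered to week 12.

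Other objections stand in part:
- Section 2.9 does not say that collection happens only in that period, and the calls appear under the heading of 2.4, so a wider reading is possible. That makes the text ambiguous. It does not make it adequate, because no text gives the calls the task of recording general adverse events.
- V2 falls before discharge, in the same inpatient phase as the sessions, and 2.9 promises close monitoring. A reader might add the V2 tests to the gap, but only V3 is clearly outside the narrow reading.
- Appendix 1, which holds the interview form, is not shown and may ask more than Sections 2.4 and 2.6 describe. An article also commonly leaves adverse-event procedures to the full protocol. However, 2.9 is not silent: it states a window, and that window is what needs correcting.
- The body of 2.9 writes out the term adverse events, so only its heading is open to misreading. In a single-center trial that risk is small.

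**Conclusion.** The point holds in a limited form. Read literally, Section 2.9 leaves non-fatal adverse events other than exacerbations without stated collection for about 92% or more of the study period, and at the V3 physical tests. For those events the low-risk statement cannot be checked.

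This rests on two assumptions: that the interventions end before discharge, as Section 2.1 and Table 1 indicate, and that the form in Appendix 1 does not already ask about general adverse events. The percentage describes time outside the window for this one class of event. It is not the share of time without any safety information, because exacerbations, symptoms and deaths are followed throughout.

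The severity is minor. The primary outcome, its analysis and the sample size are untouched.

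**What to change.** Make four changes:
1. In 2.9, replace the phrase that limits collection to the interventions with: *from randomization to the week-12 visit (V3), including study assessments*.
2. Add one fixed, neutral adverse-event question, identical in both arms, to the existing weekly calls and to V3. Section 2.4 already has the calls made by researchers blinded to group, which suits this purpose.
3. Report adverse events by arm for all randomized patients.
4. Change the heading of 2.9 to *Adverse event reporting*.

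The cost is one question on contacts that are already planned, one table in the report and a short amendment. The downside is slightly longer calls and more unrelated events to log.

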## Discussion

3

Inhaler technique is complex. Even after receiving appropriate education, many patients may use incorrect inhalation techniques due to a lack of detailed assessment of their equipment; this may reduce the efficacy of inhaled medications. Studies thus far have primarily observed the inspiratory flow rate in patients using DPIs to assess and guide optimization of inspiratory flow rate (18); however, research on the inspiratory flow rate in patients using pMDIs or SMIs is limited. We observed that when using a pMDI or SMI, most patients exhibited excessively high PIFrs (>80 L/min), increasing medication deposition in the oropharynx and thereby hindering effective drug delivery. Studies have reported that the error rate in inhalation techniques with pMDIs is as high as 86.7%, whereas that with SMIs is 58.9%. TIE primarily involves demonstration-based teaching: a physician first demonstrates the correct technique and key points to their patient; then, the patient mimics the technique under the physician's observation and guidance. However, with this technique, errors related to hand–mouth coordination and effective inhalation duration often remain undetected.

In this study, we will use sensors to monitor inhalation duration and hand–mouth coordination dynamically. With sensor feedback, physicians can provide targeted practice to address patient errors, overcoming the limitations of traditional education methods. To the best of our knowledge, this will be the first clinical study to objectively assess the entire inhalation process and offer targeted guidance for error correction. This will also be the first study to apply a visual method for inhalation technique instruction for patients with AECOPD. Visual feedback-based educational training methods have been widely applied in rehabilitation, with successful outcomes srehabilitation (24, 25), as well as in rehabilitation for pediatric cerebral palsy (26), orthopedic (27), and pain management (28).

Here, we primarily aim to observe and compare the impacts of our short-term VIT and the TIE on AECOPD frequency within 12 weeks after discharge. We anticipate that our results will provide evidence supporting the establishment of more effective inhaler technique education processes.

## Privacy protection

This study will strictly adhere to privacy protection policies regarding the collection, sharing, and maintenance of personal information for potential participants and those enrolled in the study. All personal information will be collected only after obtaining written informed consent and will be used solely for research purposes. Data will be de-identified at the time of collection, and there will be no contractual agreements limiting researchers' access to the data set. Only authorized researchers will be allowed access to the information to ensure the confidentiality and integrity of the data. During and after the study, data sharing will be limited to situations that comply with relevant regulations, ensuring the strict protection of participants' privacy. After the study concludes, personal data will be retained for a reasonable period for review or verification, but will not be used for any unauthorized purposes and will be regularly destroyed according to legal requirements.
